## Analysis items/methods

The main tabulation and analysis methods are described below. For the analysis of efficacy endpoints, analyses using various statistical methods will be performed on the data obtained, if necessary. The details of the analysis are described in a separate Statistical Analysis Plan.

### Subject background

Describe demographic variables and patient characteristics for the safety analysis population using appropriate summary statistics.

### Safety analysis

1) Analysis of adverse events and adverse events for which a causal relationship cannot be ruled out

　　For each investigational drug group (active drug group and placebo group), the number of adverse events by event (SOC and PT in the latest version of MedDRA) and by severity of the event, the number of occurrences and the percentage of occurrences (number of occurrences/number of evaluable cases) are tabulated. The same tabulation is also carried out for adverse events for which a causal relationship with the investigational drug cannot be ruled out.

2) Analysis of laboratory values

　A time trend diagram should be prepared for each subject over the entire observation period for haematological tests, blood biochemical tests and urinalysis. The number of cases and percentage of occurrence of laboratory abnormalities will be calculated.

3) Serious adverse events.

　　Narrative for each individual event.

### Analysis of efficacy endpoints

1) Primary endpoint (SARA total score after 48 weeks of treatment)

The change in SARA total score from baseline to 48 weeks post-dose is compared for the test vs control group by analysis of covariance, with baseline as the covariate and the investigational drug group (active drug group and placebo group) as the fixed effect.

2) Secondary endpoints.

SARA total score change through 48 weeks.

SARA total scores are summed for each assessment period, and the total is then subjected to a general linear mixed-effects model with the change in time (4, 8, 16, 24, 32, 36, 40 and 48 weeks) as the response variable, the investigational drug group (active drug group vs placebo group), time and baseline as fixed effects and subjects as variable effects Examine the interaction between time and investigational drug group. Multiplicity is not considered.

SARA 'walking, standing' score.

As per the method of analysis of the SARA 'total' score through 48 weeks.

SARA Scores for each item

Same analysis method for SARA 'total' scores through 48 weeks, except for the combined 'walking' and 'standing' scores for each SARA item.

Gravity body sway test

A summary of the change in total trajectory length and rectangular area (‘values after 48 weeks’ treatment’ – ‘baseline values’) obtained during the 30-second gravity body sway test is shown for each group at the time of the final assessment. Cases with a negative change are defined as improved cases, and the distribution of improved cases at the time of the final assessment is shown for each group.

TUGT.

A summary at the time of the final assessment is given for each group for the shortest time change between the two tests ('value after 48 weeks' treatment' - 'baseline value'). Cases with a negative change are defined as improved cases, and the distribution of improved cases at the time of the final assessment is shown for each group.

BDI-II.

A summary of the change in the two tests ('value after 48 weeks' treatment' - 'baseline value') at the time of the final assessment is presented for each group. Cases with a negative change are defined as improved cases, and the distribution of improved cases at the time of the final assessment is shown for each group.

CGI-S.

A summary of the amount of change in tests at each time point ('value at each time point' - 'baseline value') is presented for each group at each assessment time point. Cases with a negative amount of change are defined as improved cases, and the distribution of improved cases at each assessment time point for each group is shown.

CGI, PGI-I.

A summary at each assessment time point is given for each group.

SF-8.

A summary of the change in the two tests ('value after 48 weeks' treatment' - 'baseline value') at the time of the final assessment is presented for each group. Cases with a negative change are defined as improved cases, and the distribution of improved cases at the time of the final assessment is shown for each group.

3) Descriptive statistics, diagrams and tables

For each endpoint, calculate frequencies, proportions and 95% confidence intervals for the counts, and descriptive statistics (number of cases evaluated, mean, SD, minimum, median, maximum and 95% confidence interval) for the quantitative values, by study group and time of evaluation, as appropriate. Where necessary, drawings and tables are made.

4) Significance level

Two-sided α = 0.15 for subject background bias, one-sided α = 0.025 for the others.

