### Efficacy secondary endpoints

The following items are assessed as secondary items.

1. SARA 'total' scores after 4, 8, 16, 24, 32, 40 and 48 weeks
2. SARA 'walking, standing' scores after 4, 8, 16, 24, 32, 40 and 48 weeks
3. SARA scores after 4, 8, 16, 24, 32, 40 and 48 weeks for each item

(excluding walking and standing scores)

1. 48 weeks later Total trajectory length, rectangular area for 30 s in the gravity body sway test
2. Minimum time for Timed Up and Go Test (TUG) after 48 weeks
3. Beck Depression Inventory-II (BDI-II) total score at 48 weeks
4. Clinical Global Impression after 4, 8, 16, 24, 32, 40 and 48 weeks - Clinical Global Impression

Severity (CGI-S)

1. Clinical Global Impression after 4, 8, 16, 24, 32, 40 and 48 weeks - Clinical Global Impression

Improvement (CGI-I)

1. Patient Global Impression after 4, 8, 16, 24, 32, 40 and 48 weeks - Patient Global Impression

Improvement (PGI-I)

1. Short-Form 8 (SF-8) total score after 48 weeks

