| AJA030 PK blood sampling ^#4^ |  |  |  | ○ | ○ |  |  | 〇 |  |  | ○ | ○ | <○> |
| Identification of adverse events^#5^ |  |  |  |  |  |  |  |  |  |  |  |  |  |
| Concomitant medications and therapies |  |  |  |  |  |  |  |  |  |  |  |  |  |

#1: Performed in female subjects of childbearing potential (if pregnancy test is performed with blood, draw approximately 2 mL more blood separately).

#2: If data from pre-registration testing is within one week of the start date of administration, the data may be adopted.

#3: Only cases from Niigata University Medical and Dental Hospital should be conducted.

#4: At the visit where the blood level measurement sample is collected, the subject must be instructed to allow at least 6 hours between taking the investigational drug and collecting the sample. At the morning visit, do not take study medication before or after breakfast. At the afternoon visit, do not take the investigational drug before or after lunch. Any investigational medicines skipped for blood concentration measurement should be submitted to the investigator or collaborator as leftover medicines at the time of the visit. There is no need to take them together at the next oral dose.

#5: Adverse event assessments at the start date of dosing are carried out after the administration of theinvestigational drug.

#6: Weeks 12, 20, 28, 36 and 44 will be telephoned by the site's clinical trial staff to check status and to confirm internal medication status. Tolerance is ±7 days.

<○>: If the investigational drug is discontinued during the investigational drug administration period, it will be carried out as far as possible.

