### Observations/test items

1. **Obtaining consent**

Record the date consent was obtained.

1. **Subject background**
2. Observation period: pre-registration

2) Observations: date of birth, gender, current medical history, complications

1. **Height**

1) Observation period: pre-registration

2) Observations: height

Measure without footwear or prosthetics.

1. **Body weight**

1) Observation period: pre-enrolment, start date, 48 and 52 weeks, and at discontinuation

2) Observations: body weight

1. **Vital signs**

1) Observation period: pre-enrolment, at start of treatment, 4, 8, 16, 24, 32, 40, 48 and 52 weeks, and at discontinuation

2) Observations: body temperature, blood pressure (systolic and diastolic), pulse

Resting blood pressure and pulse rate are measured in a sitting position. Measurements should be taken using the same arm (usually the arm opposite the dominant arm) and an appropriately sized cuff.

1. **Medication log**

1) Observation period: starting date, 4, 8, 16, 24, 32, 40 and 48 weeks, and at discontinuation

2) Observations: medication records

Distribution, collection and verification of medication diaries.

1. **Haematological examination**

1) Observation periods: pre-enrolment, start date, 4, 8, 16, 24, 32, 40, 48 and 52 weeks, (at *discontinuation)

2) Observations: red blood cell count, white blood cell count, white blood cell fractions (neutrophils, lymphocytes, monocytes, eosinophils, basophils) platelet count, haemoglobin, haematocrit values

1. **Blood biochemical tests**

1) Observation periods: pre-enrolment, start date, 4, 8, 16, 24, 32, 40, 48 and 52 weeks, (at *discontinuation)

2) Observations: AST, ALT, ALP, γGTP, LDH, CPK, serum creatinine, Na, K, Ca, Cl, P, BUN, triglycerides, total cholesterol, blood sugar at any time, CRP

1. **Urinalysis**

1) Observation periods: pre-enrolment, start date, 4, 8, 16, 24, 32, 40, 48 and 52 weeks, (at *discontinuation)

2) Observations: occult blood, protein, sugar, urobilinogen

1. **Pregnancy tests (performed only on female subjects of childbearing potential).**

1) Time of observation: pre-enrolment, date of administration

2) Observations: pregnancy test (urine hCG or serum hCG)

1. **Evaluation of SARA scores.**

1) Observation periods: pre-enrolment, start date, 4, 8, 16, 24, 32, 40, 48 and 52 weeks, (at *discontinuation)

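### The secondary longitudinal SARA model lists an unmeasured week 36, names only a subject effect, and leaves the form of time open, so its one-sided 0.025 test is either liberal when progression rates vary or undefined

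*Protocol*

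**What the plan says.** Protocol section 14.3.3 (Analysis of efficacy endpoints), item 2, describes the analysis of SARA total score through 48 weeks as a "general linear mixed-effects model with the change in time (4, 8, 16, 24, 32, 36, 40 and 48 weeks". It then gives the model terms: "time and baseline as fixed effects and subjects as variable effects Examine the interaction between time and investigational drug group". No random slope or residual covariance is stated, and time is not said to be a category or a number. The same model is reused for the walking/standing score and for the remaining SARA items, with no adjustment for multiplicity.

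Item 4 of the same section sets the levels: "Two-sided α = 0.15 for subject background bias, one-sided α = 0.025 for the others". This model falls under the second part.

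The assessment times are stated elsewhere:
- The secondary endpoint list (section 8.4.4) has "SARA 'total' scores after 4, 8, 16, 24, 32, 40 and 48 weeks".
- The SARA entry in section 8.5.2 has "Observation periods: pre-enrolment, start date, 4, 8, 16, 24, 32, 40, 48 and 52 weeks, (at *discontinuation".
- Note #6 to Table 8.5.1 has "Weeks 12, 20, 28, 36 and 44 will be telephoned by the site's clinical trial staff to check status".

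Section 14.3 leaves further detail to a separate SAP.

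**The concern.** Section 8.3.4 says that the drug is expected to slow progression rather than to improve symptoms markedly. The group-by-time term in this model is therefore the analysis closest to the scientific question, and three things about it are unsettled.

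First, the model's list of times does not match the protocol's own schedule.

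Second, a subject effect alone, read as a random intercept, assumes equal variance and equal correlation at all visits. If patients decline at different rates, the spread grows with time, and the standard error of a slope difference comes out too small.

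Third, a one-sided level needs a quantity with a sign. A slope difference has one; an interaction over seven visit categories does not.

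At stake is a nominally significant secondary result on slowed progression that is weaker than its P value suggests, or one whose threshold can be argued after the fact. The same applies to the walking/standing and item scores.

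**Working it through.** **1. Times.** Section 14.3.3 lists 4, 8, 16, 24, 32, 36, 40 and 48 weeks: eight times. Sections 8.4.4 and 8.5.2 and Table 8.5.1 give 4, 8, 16, 24, 32, 40 and 48 weeks: seven on-treatment assessments. Week 36 is the one extra, and it is a telephone call. No rule fills in a week-36 value for continuing patients; the last-visit rule in section 14.2 concerns discontinued and drop-out cases only. With no data at week 36 the level drops out, and a categorical interaction keeps (2 − 1) × (7 − 1) = 6 df.

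**2. Inputs for the size of the covariance effect.** From the protocol: n = 20 per arm and T = 7 visits. The protocol gives mean progression of 1.3 to 1.6 points/year in SCA6 but no SD. Assumed: between-patient slope SD σ_b from 0.5 to 2 points/year, rating SD σ_e from 0.75 to 1.5, complete data, no treatment effect. Mid values are 1.0 and 1.0.

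**3. Continuous time, random intercept only.** The mean visit time is 172/7 = 24.57 weeks. The sum of squares about it is S = 5840 − 172²/7 = 1613.7 weeks², or 1613.7/52² = 0.597 years².

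- True variance of the slope difference: (2/n)(σ_b² + σ_e²/S).
- The model's estimate uses a pooled residual with 2n(T − 1) − 2 = 238 df. Only 2n − 2 = 38 of these carry the slope variation, so the estimate averages (2/n)(σ_e² + (38/238)Sσ_b²)/S.
- Ratio of true to estimated variance: R = (σ_e² + Sσ_b²)/(σ_e² + 0.160·Sσ_b²).
- Approximate one-sided error: 1 − Φ(1.96/√R).

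| σ_b | σ_e | R | √R | error at nominal 0.025 |
|---|---|---|---|---|
| 0.5 | 1.5 | 2.399/2.274 = 1.055 | 1.03 | 0.028 |
| 1.0 | 1.0 | 1.597/1.095 = 1.458 | 1.21 | 0.052 |
| 2.0 | 0.75 | 2.950/0.944 = 3.126 | 1.77 | 0.134 |

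Simulation over this range (8,000 null trials per setting) agrees: 0.024 to 0.133, and about 0.056 at mid values. Allowing each subject a slope brings the error to 0.022 to 0.028. When a subject effect really is the correct model, the random-intercept test holds its level (0.026).

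**4. Categorical time.** The interaction is an F test on 6 and 228 df. It rejects for any pattern of difference, in either direction, so one-sided 0.025 does not say whether its P value is compared with 0.025 or 0.05. When a subject effect is correct, the actual error is 0.025 or 0.051 respectively. Under the same assumed slope variation, at the 0.025 cut-off, it is 0.023 to 0.057: near nominal in most settings, and highest where slopes vary most and rating error is least.

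**5. Another correlation pattern.** With serial correlation of 0.7 to 0.9 per 8 weeks plus a subject effect (also assumed), the linear test gives 0.123 to 0.151 and the F test 0.057 to 0.077. A test on subject slopes stays at 0.024 to 0.027.

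**The case against.** Much can be said for the plan. Section 14.3 presents only the main methods and sends detail to an SAP that is not at hand, and residual covariance and degrees of freedom are ordinary SAP content. Naming subject as a random effect does not rule out a richer structure there. This stands, and makes the covariance point conditional. It does not remove it, because the protocol does name its random effects and names only one.

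The SDs are assumed, and the top slope SD of 2 points/year exceeds the mean progression that the protocol cites. Section 5.1.1 justifies restricting entry to SCA6 by its comparatively uniform presentation and course, so the lower part of the range may be nearer the truth. There the inflation is small. This stands too, although the same section notes that progression varies even within one disease.

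A reader might infer that the model cannot be fitted because of week 36. It can: the empty level drops out and no P value changes. Error would rise only if a value were filled in (about 0.037 for the F test if week 32 were copied forward, even when a subject effect is correct), and the protocol prescribes no such step.

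A reader might also combine the inflation of up to 0.13 with the missing direction. The two need different readings of time and cannot both apply to one test. Nor does the protocol attach a success rule to the interaction, so it cannot be said that worsening on active drug would be declared a positive result.

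**Conclusion.** The point holds in limited form. The week-36 entry is a definite contradiction, with no numerical consequence by itself. The form of time is not stated. With continuous time and a random intercept only, the slope test at one-sided 0.025 has an error of about 0.024 to 0.13 over the assumed range, and about 0.05, twice nominal, at mid values. With categorical time the one-sided level has no meaning for the 6-df test, while its error under varying slopes stays at 0.023 to 0.057.

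These sizes rest on assumed slope and rating SDs, complete data, and no better covariance in the SAP. They do not support saying that the model's P values cannot be trusted in general; the supportable statement is that they may be too small. The effect is confined to secondary analyses in a trial that the protocol calls a pilot. The primary ANCOVA of the 48-week change does not use this model.

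**What to change.** In section 14.3.3, item 2, and correspondingly in the SAP:

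- Delete 36 from the list of times.
- State that time is continuous, and give each subject a random intercept and a random slope, with Kenward-Roger degrees of freedom.
- Replace the instruction to examine the interaction by one named quantity: the 1-df group difference in slope, tested at one-sided 0.025 with the favourable direction stated.
- Apply the same wording to the walking/standing and item scores.

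The cost is a paragraph of text and no new data. Intervals for the slope difference widen by roughly the √R shown in the working: about 3% at the low end, 21% at mid values and 77% at the extreme, plus a little for fewer degrees of freedom. That widening is the uncertainty that the random-intercept model leaves out. The new test also assumes a linear trend over 48 weeks, so an early effect that later levels off would be summarised less well; the descriptive statistics by visit already planned in section 14.3.3, item 3, would show it.

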### Analysis of plasma drug concentrations.

If necessary, plasma drug concentrations are analysed for data where plasma arginine concentrations are detected.

## Interim analysis

No interim analysis will be conducted in this trial.

## Procedures for preparing and modifying statistical analysis plans.

Details of the analysis items and analysis methods will be described in a separate statistical analysis plan. The statistical analysis plan should be finalised before data fixation.

If changes or additions to the analysis plan occur after the start of the trial, the appropriateness of the changes or additions and their impact on the evaluation of the trial should be considered, and the circumstances leading to the changes or additions to the analysis plan should be described in the summary report.

# Deviations from the study protocol, amendments to the study protocol, suspension or discontinuation of the entire study

## Compliance with the clinical trial protocol

The trial will be conducted in compliance with this protocol, except in medically unavoidable cases, such as when the trial is intended to avoid immediate danger to the subject.

## Deviations from the clinical trial protocol

The investigators and sub-investigators should record all deviations from the study protocol, irrespective of the reason. The investigators and subinvestigators may deviate from the protocol if there are unavoidable medical reasons, such as to avoid immediate danger to the subject. In such cases, the investigator shall report the details and reasons as soon as possible to the head of the site.

## Revision of the clinical trial protocol.

When the investigator revises the clinical trial protocol, he/she must obtain approval from the head of the implementing medical institution. If a revision of the protocol is necessary, the investigator submits it to the head of the medical institution for approval. The clinical trial review committee, which receives a request for deliberation from the head of the implementing medical institution, should thoroughly consider the ethical, scientific and medical appropriateness of the revision when making the revision.

## Suspension or discontinuation of the entire clinical trial

### Criteria for suspending or discontinuing the entire clinical trial

The investigator should discontinue or suspend the entire clinical trial in the following cases

1. When the head of the investigational institution decides that the clinical trial should not be continued

based on the report of the investigational review committee and notifies the investigator.　Serious adverse events or other serious events causally related to the investigational drug.

1. A serious event such as a serious adverse event causally related to the investigational drug occurs.
2. When new serious information is obtained that may adversely affect the safety of subjects or the

conduct of this clinical trial.

1. When the investigator finds that the site has violated the GCP ordinance or the study protocol, thereby

interfering with the proper conduct of the study.

1. If the investigator determines that the study should be terminated or cannot be continued for any other

reason.

### Procedures for suspending or discontinuing the entire clinical trial.

In case of discontinuation according to 1) of section 14.4.1) of this protocol, the investigator should stop the entry of new subjects and discontinue the ongoing subject study as soon as possible.

In case of interruption due to 2) and 3) of the same paragraph, the investigator should promptly report the interruption to the head of the institution, and the investigator should interrupt the ongoing clinical trial for the subject at the earliest possible moment, and take appropriate measures and investigate the cause as necessary.

For subjects who have received an investigational drug, check safety after discontinuation of the investigational drug.

In the event of discontinuation of a clinical trial, the investigator should promptly report the discontinuation to the head of the implementing medical institution.

# Case report

The investigators and sub-investigators should prepare case reports on all subjects enrolled in the study with regard to the pre-enrolment examinations to be performed, the administration of the investigational drug and subsequent follow-up observations.

The EDC system will be used to generate the case report forms for this trial; the EDC system will electronically record all data history as an audit trail, including who entered the form, when it was entered, what was amended and when it was amended.

# Preservation of documents or records

## Documents or records to be kept and where they are kept.

Documents or records related to the clinical trial should be stored in accordance with the administrative communication "Administrative Communication of the Drug Evaluation and Management Division, Pharmaceuticals and Consumer Health Bureau, Ministry of Health, Labour and Welfare; Regarding documents or records related to the clinical trial" (5 July 2048) notified in accordance with the GCP Ministerial Ordinance.

## Duration of strage

1) The principal investigator and the commissioned coordinator of the clinical trial.

The self-initiator and the commissioned clinical trial coordinator should retain the documents or records pertaining to the clinical trial that should be retained by the self-initiator until the later of the following (i) or (ii).

The actions to be taken after the end of the retention period should be discussed with the investigational drug provider.

(i) The date of marketing approval (or in the case of an additional indication, the date of partial marketing approval) for the investigational drug.

(or, in the case of discontinuation or notification that the trial results will not be included in the application for approval, the date on which the decision to discontinue development was made or three years have elapsed since the date on which the notification that the results will not be included in the application was received).

(ii) The date on which three years have elapsed since the discontinuation or termination of the clinical trial.

2) Medical institutions performing

(2) The person in charge of archiving materials designated by the head of the implementing medical institution should preserve documents or records pertaining to the clinical trial that should be preserved at the implementing medical institution until the later date of the following (i) or (ii). However, in cases where the person conducting the clinical trial himself/herself requires a longer retention period than this, the implementing medical institution should consult with the person conducting the clinical trial himself/herself regarding the retention period and method of retention.

(i) The date of marketing approval (or in the case of an additional indication, the date of partial marketing approval) for the investigational drug in question (the date of development).

(or, in the case of discontinuation or notification that the trial results will not be included in the application for approval, the date on which the decision to discontinue development was made or three years have elapsed since the date on which the notification that the results will not be included in the application was received).

(ii) The date on which three years have elapsed since the discontinuation or termination of the clinical

trial.

3) Investigative Review Board (IRB)

The IRB establisher should retain records such as the SOP, list of committee members (including qualifications of each member), list of occupations and affiliations of committee members, documents submitted, minutes of meetings and letters until the later date of either (i) or (ii) below. However, if the person conducting the clinical trial himself/herself requires a longer retention period than this, the retention period and method of retention should be discussed with the person conducting the clinical trial himself/herself.

(i) Date of marketing authorisation (or date of partial marketing authorisation in the case of additional indications) for the investigational drug concerned (under development).

(or the date on which the decision to cease development was made, if the applicant was notified that the results of the trial would not be included in the application for approval, or the date on which three years have elapsed since the applicant was notified that the results of the trial would not be included in the application).

(ii) The date on which three years have elapsed since the discontinuation or termination of the clinical trial.

